### Participant timeline

#### Sample size

For the sample size, it has been estimated that about 400 workers are required with an estimated effect size of about 0.5 units of a standard deviation difference in the MHL scores between the intervention and control arms [12]. The sample size calculation is based on this assumption with a power of 80% required to detect a true intervention effect at a type I error margin of 5% with an intraclass correlation of about 0.01 for the clusters. It is also assumed that 10% of participants will drop out of the project. Since groups of participants are recruited from different sites with an average size of about 20 workers, a total of 20 sites would be required.

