### Recruitment

As aforementioned, three large companies representing different industries and a range of workplace environment have agreed to participate in the study. The study team has connection with the Human Resources Department and Senior Management of these companies. The Human Resources Departments will fully support the recruitment process with encouragement for different site offices to be part of the study. Participants will be recruited from different site offices of these companies through internal advertisement by the Human Resources Departments. Participation in the study is totally voluntary and informed consent will be obtained from participants.

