### Allocation

As a cluster randomised trial, the primary unit of randomisation is the site. For random allocation of sites, a full list of all participating office sites with some basic staffing information, such as the number and the ranks and files of staff in the office, will be obtained from the Human Resources Departments of three companies. In accordance with the preliminary information provided by these companies, the average size of site offices is about 20 staff and the deviation is small, thus the only factor for consideration in randomisation is the distribution of the site offices among these three companies. Hence, the randomisation will be stratified in accordance with the number of participating site offices across three companies. Each participating site office will be allocated to an intervention or wait-listed control arm according to a randomisation schedule generated by a central registry. The randomisation will be conducted by a qualified statistician who is blinded to the process of recruitment and the ongoing outcome assessments. The central registry will be responsible for generating the randomisation tables and will provide the information to the field staff right after the briefing session and baseline data collection via instant messaging. Participants and the site manager will be informed of the allocation at the end of the briefing session. The allocation of the randomisation codes with all information on the site office will be managed by the study coordinator. The allocation ratio between the intervention arm and the controls is 1:1.

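### The 400 workers in 20 sites cannot be reproduced from the stated inputs, which give about 167 to 240 workers, and 20 per site leaves no room for refusal or ineligibility

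*Protocol article*

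**What the plan says.** The Sample size section of the protocol article gives a complete calculation. It states that "it has been estimated that about 400 workers are required with an estimated effect size of about 0.5 units" of a standard deviation between the arms in MHL score, with "a power of 80% required to detect a true intervention effect" at a 5% type I error, "with an intraclass correlation of about 0.01 for the clusters", and 10% dropout. The number of sites follows from the cluster size: "with an average size of about 20 workers, a total of 20 sites would be required".

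Three other sections bear on the cluster size. The Allocation section reports, from preliminary company information, that "the average size of site offices is about 20 staff and the deviation is small", and sets a 1:1 ratio. The Recruitment section states that "Participation in the study is totally voluntary". The participant exclusion criteria remove staff who have already had similar psychoeducation training or a similar intervention.

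**The concern.** An ICC of 0.01 with 20 per site inflates a simple two-group sample size by only 19%. A half-SD effect at 80% power needs roughly 126 people before inflation, so a total of 400 looks far too large for these inputs. If the paragraph does not close, a reader cannot tell what the trial was powered for, or whether the 80% is right, generous or optimistic.

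The second issue is yield. The 20 participants per site used to obtain 20 sites is the same number as the staff in an average office. The 10% allowance covers loss after enrolment. It does not cover workers who decline or are excluded beforehand.

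**Working it through.** **Inputs from the document.** Effect 0.5 SD, power 80%, type I error 5%, ICC 0.01, 20 workers per site, dropout 10%, allocation 1:1. Sidedness is not stated, so two-sided is assumed.

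**Step 1: attempt to reproduce 400.**
- Per arm, individually randomised: 2(1.96 + 0.842)² / 0.5² = 62.8, so 63 (64 with the t correction). Total 126 (128).
- Design effect: 1 + (20 − 1) × 0.01 = 1.19.
- With dropout: 126 × 1.19 / 0.9 = 166.6, so 167. With 128: 169.2.
- Sites: 166.6 / 20 = 8.3, so 9, or 10 for equal arms.

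The stated 400 is 400 / 167 = 2.4 times this.

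**Step 2: allow for few clusters.** A t-test on cluster means with (sites − 2) degrees of freedom first reaches 80% at 10 sites with 20 analysed per site (81.0%, 200 workers). With 18 analysed per site after dropout, 10 sites give 77.5% and 12 give 86.4% (240 workers enrolled). On this basis 400 is 1.7 to 2.0 times the requirement.

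**Step 3: other variants at ICC 0.01.**

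| Variant | Workers enrolled |
|---|---|
| One-sided 5% | 132 |
| 18 per site in the design effect | 164 |
| Dropout as N × 1.10 | 165 |
| 90% power | 225 |
| 5% split over six outcomes | 257 |
| 95% power | 275 |
| Change score, baseline correlation 0 | 333 |

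None reaches 400.

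**Step 4: what would give about 400?** Changing one input at a time:
- ICC 0.10: design effect 1 + 19 × 0.10 = 2.90; 126 × 2.90 / 0.9 = 406 (402 with N × 1.10; 412 starting from 128), or 20.3 sites. Solving for exactly 400 gives ICC 0.098.
- Effect 0.32 SD: 154 per arm; 308 × 1.19 / 0.9 = 407.
- Power 99%: 147 per arm; 294 × 1.19 / 0.9 = 389.

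**Step 5: power of the 20-site design for 0.5 SD.** The variance of the difference in cluster means is SE² = 4[ICC + (1 − ICC)/m] / 20, with m analysed per site. Full uptake gives m = 20 × 0.9 = 18. Uptake of 60% is an assumption, not a figure from the document; it gives 240 enrolled, 216 analysed and m = 10.8.

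| ICC | Uptake | SE | Power, z | Power, t (18 df) |
|---|---|---|---|---|
| 0.01 | 100% | 0.114 | 99.2% | 98.5% |
| 0.01 | 60% | 0.143 | 93.9% | 91.2% |
| 0.05 | 100% | 0.143 | 93.7% | 90.9% |
| 0.05 | 60% | 0.166 | 85.3% | 81.2% |
| 0.10 | 100% | 0.173 | 82.3% | 77.9% |
| 0.10 | 60% | 0.191 | 74.3% | 69.5% |

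At ICC 0.01 and full uptake, the effect detectable with 80% power is 2.802 × 0.114 = 0.32 SD (z), or 0.34 SD (t).

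**Step 6: yield.** 20 sites × about 20 staff = 400, the whole average headcount. Enrolling 400 from 20 sites therefore needs about 100% eligibility and consent.

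Steps 2 and 5 are post-only comparisons of cluster means. They are not the planned mixed model of change from T0 to T1.

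**The case against.** **The misprint reading.** A reader might infer that 0.01 is a slip for 0.10, because that change reproduces both the workers and the sites. The match is close, but Step 4 shows that a smaller effect or a higher power would also land near 400. The document does not show which input was used, so this remains one possibility.

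**The underpowering reading.** A reader might also infer that the trial falls below 80% whichever ICC is right, or that it has no slack at all. The figures do not support that. At the printed ICC of 0.01 the design is oversized, and 60% uptake still leaves about 91 to 94%. At ICC 0.10 the z figure is 82.3%, consistent with the stated 80%, and it remains 80.9% at 90% uptake. The shortfall at full uptake appears only with the 18-df t-test. The protocol does not name that test: it plans a generalised linear latent and mixed model, and its stratification by company leaves the degrees of freedom unsettled.

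**The planned analysis differs from the check.** Its power depends on the T0 to T1 correlation, which is not given and could move power either way. This stands, so the power figures here should not be copied into the protocol as the design's power. It does not rescue the 400: even a change score with zero correlation gives 333.

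**Uptake.** The headcount is preliminary and approximate, and nothing caps recruitment at 20 sites, so offices could be added. That is fair, and it makes the yield issue secondary. It does not alter the fact that the paragraph derives 20 sites by counting every member of staff.

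**Conclusion.** The concern holds as an internal inconsistency. The printed inputs give about 167 to 169 workers, or 200 to 240 with a cluster-level small-sample test, against a stated 400. Conversely, 400 in 20 sites at ICC 0.01 has about 98 to 99% power for 0.5 SD, not 80%. At least one of the ICC, effect size or power is therefore misstated, and the document does not allow a reader to say which.

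The yield assumption of near-complete eligibility and consent is a second, smaller fault. Its effect on power depends on the ICC: slight at 0.01, but material near 0.10, where an assumed 60% uptake gives about 74% (z) or 70% (t).

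These results assume a two-sided test, equal cluster sizes and a post-only analysis. Neither the validity of the randomisation nor the type I error is in question, and the documents do not establish that the trial is underpowered.

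**What to change.** Restate the Sample size paragraph so that it reproduces its own result:
- Give the ICC, effect size, power and sidedness actually used, and correct whichever printed value is wrong.
- Write the yield as sites × staff per site × assumed uptake, with uptake covering both eligibility and consent.
- State the power of the 20-site design at that uptake, naming the method and any small-sample correction. If it is computed for the planned repeated-measures model, give the assumed T0 to T1 correlation. If figures like those above are used, label them as post-only cluster-mean approximations.

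The cost is rewording one paragraph. The stated power may change in either direction. No added participants or sites are requested.

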### Recruitment

As aforementioned, three large companies representing different industries and a range of workplace environment have agreed to participate in the study. The study team has connection with the Human Resources Department and Senior Management of these companies. The Human Resources Departments will fully support the recruitment process with encouragement for different site offices to be part of the study. Participants will be recruited from different site offices of these companies through internal advertisement by the Human Resources Departments. Participation in the study is totally voluntary and informed consent will be obtained from participants.

### Consent

Informed consent will be obtained from potential participants during the briefing session conducted by the senior social worker at each site once the site managers have agreed to partake in the study. At the briefing session, information on the study and the intervention programme will be provided to all potential participants verbally and as a written information sheet (Additional file 3). Willing participation in the study will be solicited from potential participants by signing the consent form (Additional file 2). Upon consenting, participants will be asked to provide their mobile number as the unique identifier of the individual so that data collected at different time points of the study could be linked. Potential participants who are unable to attend the briefing session can contact the research team directly prior to consenting. The same consent process will be applied to all sites.

### Allocation

As a cluster randomised trial, the primary unit of randomisation is the site. For random allocation of sites, a full list of all participating office sites with some basic staffing information, such as the number and the ranks and files of staff in the office, will be obtained from the Human Resources Departments of three companies. In accordance with the preliminary information provided by these companies, the average size of site offices is about 20 staff and the deviation is small, thus the only factor for consideration in randomisation is the distribution of the site offices among these three companies. Hence, the randomisation will be stratified in accordance with the number of participating site offices across three companies. Each participating site office will be allocated to an intervention or wait-listed control arm according to a randomisation schedule generated by a central registry. The randomisation will be conducted by a qualified statistician who is blinded to the process of recruitment and the ongoing outcome assessments. The central registry will be responsible for generating the randomisation tables and will provide the information to the field staff right after the briefing session and baseline data collection via instant messaging. Participants and the site manager will be informed of the allocation at the end of the briefing session. The allocation of the randomisation codes with all information on the site office will be managed by the study coordinator. The allocation ratio between the intervention arm and the controls is 1:1.

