### Blinding

Allocation is concealed from the study Principal Investigator and the study team at the time of the participants’ inclusion in the trial; however, field staff and the project coordinator collecting and managing the data will not be blinded to participants’ allocation. In no circumstances should the blinding be broken to the study team.

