#### Workplace environment scan

The workplace environment scan will be conducted by the senior social worker using the Moos Work Environment Scale (WES) [16]. Data will be collected during the briefing session through an online survey. Participants from each site will be asked to fill in the survey on site at the end of briefing session. Participants who have consented but miss out on the briefing session can contact the project team. They will be guided to fill in the baseline survey through a telephone call. Incomplete surveys will be identified during the data management process right after baseline data collection. Participants who have not completed the survey will be contacted via instant messaging or emails to encourage a re-attempt of the survey.

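### A site's arm is announced at the end of its briefing, while consent and baseline remain open for absentees and incomplete responders, so some can join or answer T0 knowing their arm

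*Protocol article*

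**What the plan says.** The intended order is clear. The Methods part of the Abstract and the Pre-randomisation process section put enrolment, consent and the T0 assessment before allocation.

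The Allocation section fixes when the arm becomes known. The central registry "will provide the information to the field staff right after the briefing session and baseline data collection via instant messaging", and "Participants and the site manager will be informed of the allocation at the end of the briefing session".

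Three catch-up routes are also described:

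- **Consent.** "Potential participants who are unable to attend the briefing session can contact the research team directly prior to consenting" (Consent section).
- **Baseline for absentees.** "Participants who have consented but miss out on the briefing session can contact the project team". How these people then give their baseline answers is also stated: "They will be guided to fill in the baseline survey through a telephone call" (Workplace environment scan section).
- **Re-attempts.** "Incomplete surveys will be identified during the data management process right after baseline data collection", and "Participants who have not completed the survey will be contacted via instant messaging or emails to encourage a re-attempt of the survey" (same section).

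The Outcome measures section under Data collection methods has participants complete the baseline outcome survey in the same sitting as the environment scan survey. The Statistical analysis plan section bases the primary comparison on the mean change in mental health literacy score from T0 to T1.

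**The concern.** Participants cannot be blinded to this programme and the outcomes are survey answers. Keeping the arm unknown until enrolment and baseline are complete is therefore the main protection against bias at entry. The catch-up routes have no stated closing time, while disclosure is tied to the end of the briefing.

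Two things are at stake. First, joining is voluntary. An office assigned to immediate training gives late staff a different reason to join from an office told to wait 3-4 months (Control group section). The late joiners may then differ between arms, and intention-to-treat analysis does not correct who was recruited. Second, a T0 answer given with the arm known may be shifted by that knowledge. Because the primary analysis is a change from T0, the shift passes into the estimated effect. The analysis section also chooses adjustment variables from observed baseline differences, so a distorted baseline could influence the model as well.

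**Working it through.** **Order of events at one site, as written**

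1. The briefing is held, attenders consent, and they complete the scan survey and T0 outcomes (Pre-randomisation process; Consent; Workplace environment scan; Outcome measures).
2. The registry sends the allocation to field staff, and participants and the manager are told before the briefing closes (Allocation).
3. Incomplete surveys are identified after baseline collection and those participants are prompted to try again (Workplace environment scan). This step follows the point at which allocation is released.
4. Staff who were not at the briefing contact the team, consent if they have not done so, and complete baseline by telephone. No time limit relative to step 2 is given (Consent; Workplace environment scan).

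Attenders who finish at step 1 are protected. Step 3 comes after disclosure, and step 4 may. Nothing in the article closes steps 3 and 4 before step 2, or delays step 2 until they are done.

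**Illustrative size**

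The plan gives no figure for this point, so the inputs are assumptions. Let *f* be the share of participants whose T0 is given after disclosure, and *s* the difference between arms in their T0 answers caused by knowing the arm. The contrast in change is

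(T1 intervention − T1 control) − (T0 intervention − T0 control),

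so an error of *f* × *s* in the T0 difference moves the contrast by the same amount with the opposite sign.

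| Late share *f* | *s* = 0.2 SD | *s* = 0.3 SD |
|---|---|---|
| 10% (40 of 400) | 0.02 SD | 0.03 SD |
| 30% (120 of 400) | 0.06 SD | 0.09 SD |

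Against the planned 0.5 SD (Sample size section) this is 0.02/0.5 = 4% to 0.09/0.5 = 18%. The direction is not known.

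**Cost in power if late joiners are left out**

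Inputs from the Sample size section: 400 workers, 20 sites, effect 0.5 SD, intraclass correlation 0.01, 10% dropout. Two-sided 5% is assumed. With a share *f* left out, the number analysed is N = 400 × (1 − *f*) × 0.9, the site size is m = N/20, the design effect is 1 + (m − 1) × 0.01, and power is Φ(0.5 × √(n/2) − 1.96), where n is N/2 divided by the design effect.

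| Left out | N | m | Design effect | Power |
|---|---|---|---|---|
| none | 360 | 18.0 | 1.170 | 0.992 |
| 10% | 324 | 16.2 | 1.152 | 0.987 |
| 20% | 288 | 14.4 | 1.134 | 0.979 |
| 30% | 252 | 12.6 | 1.116 | 0.964 |

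The stated inputs do not reproduce the planned total of about 400: 63 per arm × 1.19 = 75, so 150 in all, and 150/0.9 = 167. That is a separate matter. It bears here only in that, on the plan's own assumptions, a few late volunteers can be spared.

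**The case against.** The main route is protective. Most staff are meant to consent and answer T0 on site before the arm is released, so any exposure is confined to stragglers. The article is also a condensed version, and a cut-off for stragglers might stand in the full protocol. Wait-listed staff expect the same programme within months, which narrows the difference in incentive, and no mechanism is documented for how knowing the arm would shift literacy answers. All of this limits the likely size. It does not remove the problem, because the article does more than omit a detail: it fixes an early disclosure and separately describes routes that can run past it.

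Several stronger readings are tempting but not supported:

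- *That the Blinding section is contradicted.* It conceals allocation from the Principal Investigator and study team and states in the same sentence that "field staff and the project coordinator collecting and managing the data will not be blinded". Telling participants and managers does not contradict this.
- *That unblinded staff take the telephone baseline.* The text does not say who guides the call.
- *That every late participant knows the arm.* The text permits this and does not prescribe it. Some absentees could consent or answer before the briefing ends.
- *That late joiners who simply score differently would bias the effect by a calculable amount.* A stable difference appears at both T0 and T1 and largely cancels in the change. Selection matters through late joiners who would change differently, and nothing in the documents allows that to be sized.
- *That the coordinator can see unreleased codes.* Managing the codes may refer to handling after release.

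**Conclusion.** The point holds in a limited form. Followed as written, the plan allows some participants to enrol, or to give T0 outcome answers, after their site's arm has been announced, against its own intended order. The consequences are a risk of recruitment that differs by arm and of arm-influenced baseline values entering the primary change analysis.

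The size is unknown because the number of late participants is not given. The range of 0.02-0.09 SD is an illustration. It rests on an assumed late share of 10-30%, an assumed shift of 0.2-0.3 SD, and a change analysis in which T0 error carries over in full. The upper end combines the two largest assumptions. This does not show that the trial will be materially biased. It shows an avoidable opening that cannot be repaired once recruitment is done, and that is cheap to close.

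**What to change.** State in the Allocation section that a site's allocation goes to field staff, manager and participants only after a short baseline window of fixed length following the briefing has closed and the site's list of consented participants with T0 data is locked. Absentee consent, telephone baseline and re-attempts all take place inside that window. Staff who consent later may take the programme but are not in the primary analysis set. Membership of that set is then settled before anyone at the site knows the arm. Any T0 completed after disclosure is flagged and examined in a sensitivity analysis, for example by treating those values as missing and using the multiple imputation already planned.

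The cost is a few days between briefing and start at each site, the loss of a few late volunteers from the primary analysis, and a matching sentence defining the analysis set. On the plan's own inputs, power stays at about 0.98 even with 20% left out. If the full protocol already contains such a cut-off, stating it beside the disclosure rule is enough.
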